### Quality Control

Our study team is an experienced group consisting of a senior expert in the field of geriatric care, three graduate students specializing in geriatric care, and nursing home professional nurses. Experienced nursing home professional nurses and the researcher on the team will be responsible for recruiting participants. Participants who meet the inclusion criteria will be screened, informed of the study details by the researcher, and asked to sign a consent form if they agree to participate. If there are complex clinical issues, our researchers, nursing specialists, and nursing home professional nurses will work together to find solutions.

The investigators will provide uniform and standardized training to all personnel implementing the intervention, and will conduct group training and related assessments on the use of the scale to ensure that implementers are familiar with the content and master the use of the scale, and that it will be tested and collected on the spot to ensure the validity and recall of the questionnaire.

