### Study Design

A multicentre, single-blind, three-arm, randomized controlled trial will be conducted to assess the effect of reminiscence therapy combined with memory specificity training on improving autobiographical memory in older adults and further assess the effect on improving depressive symptoms in older adults. Based on the screening criteria, 78 participants will be recruited from three nursing homes in the provincial capital of China, and participants will be randomly divided into three groups in a 1:1:1 ratio. Participants in the first group will receive a 4-week intervention with reminiscence therapy, participants in the second group will receive a 4-week intervention with reminiscence therapy combined with memory specificity training, and participants in the third group will receive 4 weeks of usual care, followed by a 24-week follow-up.

Data will be collected at baseline, immediately postintervention, 1 month, 3 months, and 6 months postintervention. The study design is shown in Fig. 1. After the intervention, the same instructions will be given to a third group to ensure that more older adults benefit.

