### Randomization and blinding

Among all nursing homes with similar conditions in the capital city of a province in China, three nursing homes will be selected to be included in this study by using the random number table [48], and then the envelope method will be used to determine which nursing home would implement which intervention. After obtaining the nursing homes’ consent to participate, the allocation will be kept concealed by random grouping. This work will be done independently by individuals who are not involved in the study and who keep a strict allocation sheet.

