#### Reminiscence therapy

The group will implement group reminiscence therapy with 4 reminiscence phases. Each subgroup will consist of 1 implementer and 6–7 participants and will focus on 1 growth phase once a week for 90 min each time. The implementer will be responsible for guiding and encouraging the group members to freely recall past experiences and ensuring that each participant speaks for at least 10 min. The intervention details are shown in Table 2.

**Table 2 Tab2:** Intervention details

Sessions	Content
1st (week 1)	**Life stage**: Childhood (0–18 years) **Topic**: family, study experience, holidays etc. **Members**: 1 implementer and 6–7 participants. **Duration**:90 min. **Method**: The implementer will be responsible for guiding and encouraging the group members to freely recall past experiences and ensuring that each participant speaks for at least 10 min.
2nd (week 2)	**Life stage**: Young adulthood (18–25 years) **Topic**: friendship, education, technology change etc. **Members**: 1 implementer and 6–7 participants. **Duration**:90 min. **Method**: The implementer will be responsible for guiding and encouraging the group members to freely recall past experiences and ensuring that each participant speaks for at least 10 min.
3rd (week 3)	**Life stage**: Adulthood (25–65 years) **Topic**: spouse, parenting, professional experience etc. **Members**: 1 implementer and 6–7 participants. **Duration**:90 min. **Method**: The implementer will be responsible for guiding and encouraging the group members to freely recall past experiences and ensuring that each participant speaks for at least 10 min.
4th (week 4)	**Life stage**: Old age (over 65 years) **Topic**: philosophy of life Looking back etc. **Members**: 1 implementer and 6–7 participants. **Duration**:90 min **Method**: The implementer will be responsible for guiding and encouraging the group members to freely recall past experiences and ensuring that each participant speaks for at least 10 min.

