#### Autobiographical memory

Participants’ autobiographical memory will be measured by the Autobiographical Memory Test. The Autobiographical Memory Test was developed by Williams and Broadbent in 1987 [52] and is a test that is currently widely used in clinical research; this assessment utilizes a cue word technique in which subjects review past personal experiences through cue words that contain five positive cue words, five neutral words, and five negative cue words. Participants will be given two neutral practice words to practice before the formal test. They will be asked to verbally recall memories related to cue words within 1 min during the formal administration of the test, and the implementer will record the recollections in the form of a transcript. The scoring will be performed by two researchers who are not involved in the administration of the test. The two scorers will classify the participants’ recollections into four categories: specific memory, generalized memory, vocabulary association or nonrecollection and nonresponse, and the scoring will be based on the number of cue words recalled by the participants. Since Chinese scholars have translated the cue words in this test into Chinese, composed a vocabulary database and rated the valence of the vocabulary, the Chinese version of the ATM will be used in this study [53], which has a high internal consistency and a reliability test Kappa coefficient of 0.81–0.95 [54]. Cue words that will be used in the assessments and training are shown in Table 5.

**Table 5 Tab5:** Cue words

pre-test	post-test	follow-up
Strong	Deep Love	Honest
History	Books	Relaxed
Fear	Sadness	Friendly
Security	Interesting	Guilty
Individual	Oval	Nervous
Failure	Reject	Desperate
Excitement	Lively	Patience
Caution	Bread	Agile
Solitude	Doubt	Culture

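### The trial is called single-blind without naming who is blinded, and the text suggests that session leaders also handle the scales and record the memory test

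*Protocol article*

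**What the plan says.** - **Label.** Study Design states: "A multicentre, single-blind, three-arm, randomized controlled trial will be conducted". The Abstract and the Discussion repeat the label. None of them says who is blinded.
- **Randomization and blinding.** On masking, this section offers only that "the allocation will be kept concealed by random grouping", which concerns concealment of the allocation. It also says that "the envelope method will be used to determine which nursing home would implement which intervention", so each home delivers one arm.
- **Who leads the sessions.** Under Reminiscence therapy, "Each subgroup will consist of 1 implementer and 6–7 participants", and "The implementer will be responsible for guiding and encouraging the group members to freely recall past experiences".
- **Who records the memory test.** Under Autobiographical memory, "the implementer will record the recollections in the form of a transcript". Scoring is separate: "The scoring will be performed by two researchers who are not involved in the administration of the test". Nothing is said about whether these two know the arm.
- **Who handles the scales.** A single sentence in Quality Control covers training of the staff who carry out the intervention and training in the use of the scale, "to ensure that implementers are familiar with the content and master the use of the scale". It adds that questionnaires are completed and gathered there and then. No separate assessor is named for the GDS, RRS or IPA.

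**The concern.** Blinding protects an outcome only if the blinded person can influence its value. GDS, RRS and IPA are subjective. Residents cannot fail to know whether they attend weekly 90-minute group sessions or receive routine care only. If the person who led those sessions then hands out and collects the scales, residents in the active arms have a reason to answer kindly that residents under usual care do not have, since usual care has no session leader. Such a bias would differ by arm and would favour the active arms, above all against usual care.

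The memory test is exposed in a second way. In the combined arm the session leader prompts residents for more specific and complete recollections, which is the property the test measures. If the same person gives the test, that habit of prompting could carry over into what is elicited and written down. Separate scorers can score only what is on the transcript.

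A reader of the results would also take the single-blind label as a safeguard on the outcomes, and the text does not show that it is one.

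**Working it through.** The plan gives no figure to reproduce on this point, so the check is mainly textual.

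**1. Who is blinded?** The candidates are the participant, the session leader, the outcome collector and the memory-test scorer.

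| Party | What the article says | Blind? |
|---|---|---|
| Participant, active arm against usual care | Weekly group sessions against routine care | Cannot be |
| Participant, one active arm against the other | Same process and content, apart from the added prompting, in different homes | Possible; not stated |
| Session leader | Delivers the arm | Cannot be |
| Collector of GDS, RRS, IPA | Scale training is for implementers; no separate assessor named | Not stated; unlikely |
| Recorder of the memory test | The implementer | Not stated; unlikely |
| Memory-test scorers | Separate from administration | Possible; not stated |

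**2. Are leader and collector the same person?** Reminiscence therapy and Table 2 use implementer for the session leader. Autobiographical memory uses the same word for the recorder of the test. Quality Control uses it for the people trained on the scales, in a sentence that opens with the staff delivering the intervention. The team is small: one senior expert, three graduate students and nursing-home nurses. The natural reading is an overlap of roles. It remains an inference.

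**3. Does a separate assessor restore masking?** Eligibility and recruitment asks for 26 residents per home, and 3 × 26 = 78, which agrees with one arm per home. At 6 to 7 per subgroup, 26 residents make about four subgroups (26/7 = 3.7; 26/6 = 4.3), all in the same arm. An assessor swapped between subgroups is no longer the resident's own leader but still knows the arm. An assessor from elsewhere knows which home this is and can readily infer it.

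**4. Can the scorers be masked?** Arm and home can be removed from a transcript. Stage cannot be hidden fully, because Table 5 lists different cue words for pre-test, post-test and follow-up.

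**5. Illustration only.** Suppose that expectation or courtesy shifts the active-arm GDS by δ standard deviations with no true effect. The document gives no δ; 0.2 to 0.3 is an assumption. With n = 24 per arm (Sample size calculation) and a normal approximation:

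- λ = δ√(n/2) = δ√12, which is 0.69 at δ = 0.2 and 1.04 at δ = 0.3.
- Two-sided rejection rate = Φ(−1.96 + λ) + Φ(−1.96 − λ), which is 0.103 + 0.004 = 0.107 and 0.179 + 0.001 = 0.180. At δ = 0 it is 0.05.
- Relative to the planned effect of 0.8, the shift is 0.2/0.8 = 25% to 0.3/0.8 = 37.5%.

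This treats residents as independent. With homes allocated to arms, the 5% starting point does not describe this trial. The figures show only that a modest shift would matter.

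**The case against.** The strongest reply is that the overlap of roles rests on one loosely used word. Under the combined therapy the person guiding the sessions is called the researcher. In the memory-test paragraph, implementer may mean whoever runs the test, and in the usual-care home it cannot mean that home's session leader, because there are no sessions. Quality Control may describe two separate training activities, and it does not say who gathers the questionnaires. This stands: a reader might infer that session leaders certainly collect the outcomes, and the article does not establish that. It does not remove the point, because on-site assessors are likely to know the arm from the home whoever they are.

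A reader might also infer that nobody is blind, or that the single-blind claim is false. Neither is shown. Residents may not know which of the two active versions they receive, and that comparison is one of the study's hypotheses. The scorers may be masked. The label is undefined, not disproved.

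The separate scorers are a real safeguard, and whether they are masked to arm is the kind of detail a condensed article may leave to the full protocol. That too stands, and scorer masking alone would not be a finding.

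Finally, the primary outcome is self-reported and the limitations concede some self-report bias. Any influence of the collector on the GDS is therefore indirect. But self-report leaves only participant blinding as a protection, which is unavailable against usual care, and the limitations do not mention who collects the data.

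**Conclusion.** The point holds in a limited form. The single-blind claim has no stated content, and the sections that do bear on outcome collection suggest that unblinded session leaders handle the scales and record the memory test. It reaches all four outcome measures (GDS, memory test, RRS, IPA) at all four post-baseline visits. It matters most for the two comparisons with usual care and less clearly for the comparison between the active arms.

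The conclusion assumes that implementer means the same role throughout, and that homes are allocated to arms as Randomization and blinding describes. If the first assumption fails, the undefined label and the likely knowledge of arm on site remain.

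The size of the bias cannot be estimated from the document. The 0.2 to 0.3 SD shift is an assumption and must not be read as an estimate. The change is worth making because it is cheap and either reduces a bias in the primary outcome or corrects what the trial may claim.

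**What to change.** 1. **Separate the roles.** With the existing team, state that nobody collects T1 to T4 GDS, RRS, IPA or memory-test data from residents whose sessions they led. Use different words for session leader and assessor in Autobiographical memory and Quality Control. This limits courtesy bias; it does not guarantee masking, since the home gives away the arm.
2. **Redact the transcripts.** Pass memory-test transcripts to the two existing scorers with arm and home removed, and say so. Do not claim masking of time point, because the cue words reveal the stage.
3. **Define the label.** In Randomization and blinding, name who is blind and for which outcome and comparison. Do not describe the GDS, RRS and IPA comparisons with usual care as blinded.

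The cost is some scheduling, since assessors must be matched to residents they did not treat, plus redaction of transcripts and a less favourable description of the blinding. No new assessor is needed, provided the team can cover the roster; the article does not say how many people lead sessions, so this should be checked.

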## Discussion

Depression in older people is a global public health problem. According to the World Health Organization, adults between the ages of 55 and 74 years are the people most affected by depression [59]. Late life depression (LLD) is a common disabling disorder, with a prevalence ranging from 9–45% [60], especially during the COVID-19 pandemic. Older people may be more vulnerable to the mental health effects of the pandemic and have a significantly increased risk of dementia, whether directly from the infection itself or indirectly from infection-preventive measures [61]. Cost-effective psychological interventions are urgently needed to improve depression in older adults.

Reduced autobiographical memory with increased overgeneral memory as a cognitive marker of depression is not only evident in individuals with a history of depression, but also predicts subsequent increases in symptoms [62]. Fortunately, studies have shown that this overgeneral memory is not a fixed feature of an individual’s memory style but can be modified [63]. In high-risk populations without a clinical diagnosis, the benefit of memory specificity training may be reflected in preventing further severity of symptoms [64], but its effectiveness alone is modest and short-lived [65].

Reminiscence therapy has received increasing attention as a psychotherapy that has been developed over a long period of time and has a more mature intervention model. It helps older adults gradually recall memories of past experiences and unresolved conflicts through many therapeutic aspects, alleviates negative emotions by integrating all past positive and negative experiences, fosters a sense of security, and helps support the intrinsic capacity of older adults to age healthily [28]. Therefore, we will implement a multicentre, single-blind, three-arm parallel group randomized controlled trial to investigate whether the combination of the two therapies can further confirm the role played by autobiographical memory in the overall improvement of depressive symptoms in older adults while promoting the emergence and implementation of more therapies targeting autobiographical memory.

However, this study still has limitations. First, the sample size is small, and the population is limited to three nursing homes, so the results may not be fully generalizable. Second, the study will be conducted by different team members, and the consistency of implementation may be questionable. Finally, the scales used in the study are partially self-reported scores, which may be subject to some bias.

In conclusion, we have designed a study combining two psychological interventions with the expectation that their combined use would increase the improvement of depressive symptoms in older adults. Based on this evidence, we believe that this intervention program will be able to increase autobiographical memory and improve depressive symptoms in older adults. If the intervention produces significant positive effects, the findings will also potentially provide valuable evidence to facilitate and provide feasible strategies to further promote healthy ageing.

## Data Availability

Not applicable.

## List of abbreviations

ATM: Autobiographical Memory
OGM: Over-general Memory
RT: Reminiscence Therapy
MeST: Memory Specificity Training
